# CLINICAL STUDY PROTOCOL

Title: Safety and efficacy of levosimendan in patients with acute myocardial infarction complicated by symptomatic left ventricular failure

Sponsors protocol nr: 0105

Vs. 02

Revised: 2004-01

Registered at : www.clinicaltrials.gov

**Phase** III study.

**Design:** Double blind, placebo-controlled study with parallel groups in patients undergoing acute percutaneous-coronary intervention (PCI) for acute myocardial infarction complicated with decompensated, symptomatic heart failure. The study includes a prospectively defined subgroup of patients in cardiogenic shock.

**Purpose:**

Evaluate the safety and efficacy of a 24-hour infusion with levosimendan compared to placebo, in patients with acute myocardial infarction complicated with decompensated heart failure after acute revascularization by PCI.

**Responsible for the study**: Department of Cardiology, Ullevaal University hospital

**Principle investigator:** [name] [name] (MD, PhD)

## PROTOCOL SUMMARY

| Phase | III |
| --- | --- |
| **Design** | Double blind, placebo-controlled study with parallel groups in patients with acute PCI treated myocardial infarction complicated with decompensated heart failure. Prospectively defined subgroup of patients in cardiogenic shock. |
| **Purpose** | Evaluate the safety and efficacy of a 24-hour infusion with levosimendan compared to placebo, in patients with acute myocardial infarction complicated with decompensated heart failure and in a subgroup of patients in cardiogenic shock. |
| **Primary endpoint** | **Efficacy parameters**:   - - Changes from baseline to 5 days in Wall motion score-index measured by echocardiography.   - Changes from baseline to 5 days in BNP (Brain natriuretic peptide).   - Clinical composite at 5 days after start of the study drug infusion, according to the physician’s global assessment measured as change from baseline to 5 days.   **Safety parameters**: Number of patients developing:   - - Hypotension: BP < 90 mm Hg or a drop in mean arterial BP > 10 mm Hg in patients with cardiogenic shock.   - Tachycardia (heart rate above 120).   - Atrial fibrillation.   - Ventricular arrhythmia (VT, VF, TDP).   - Ischemic episodes (ECG changes or chest pain demanding treatment). |
| **Secondary endpoints** | Efficacy parameters  - MACE: Time to death, non-fatal myocardial infarction or revascularization of the infarct related artery during the first 6 weeks and 6 month after start of the study drug infusion. - Changes from baseline to 24 hours in Wall motion score-index measured by echocardiography - Changes from baseline to 6 weeks in Wall motion score-index measured by echocardiography - Changes from baseline to 24 hours in BNP - Changes from baseline to 6 weeks in BNP - Number of days in intensive or coronary care unit. - Total number of days hospitalised. - Time to re-hospitalization for decompensated heart failure. - Clinical composite at 24 hours after the start of the study drug infusion, according to the physician’s global assessment measured as change from baseline to 24 hours. - Infarct size measured at 6 weeks by gated spect (radioisotope technique). - Changes of inflammation markers, haemostasis parameters and serum lactate from baseline to 24 hours, 5 days and 6 weeks. - Changes of E/E` ratio measured by echocardiography from baseline to 24 hours and 5 days.   **In a subgroup of patient *with* cardiogenic shock:**   - Improvement of hemodynamic parameters (CI, PCWP, and SVRI) from baseline to 24 and 48 hours. - Number of days on intra-aortic-balloon counter pulsation treatment (IABP). - Improvement of central venous oxygen saturation. - Improvement of kidney function measured as creatinine clearance. - Total mortality (number of patients alive at discharge).   **In patients *without* cardiogenic shock:**   - - The patient’s global assessment VAS-scale at 24 hours and at 5 days after the start of the study drug infusion.   - Need for IV inotropes, at the clinicians decision, after start of the study drug infusion. |
| **Number of patients** | 60 patients at 1 centre.  A minimum of 14 patients in cardiogenic shock will be included. |
| **Patient group**  **Major inclusion criteria:** | Patients who are hospitalised with acute ST-segment elevation myocardial infarction subject to acute PCI  *Or*  Patients with non-ST segment elevation myocardial infarction subject to PCI within 72 hours after start of chest pain.  *and all of the following (1-3)*   - - Revascularization by PCI with opening of an occluded coronary artery or balloon dilatation of a stenotic coronary artery presumed to be culprit lesion.   - Depressed contractility of the left ventricle (left ventricle ejection fraction < 40 %) assessed by echocardiography   - Dyspnoea at rest at screening and *at least* one of the following signs of left ventricular failure (within 48 hours after PCI):     - Pulmonary edema     - Signs of marked pulmonary congestion on chest x-ray     - Need for CPAP or mechanical ventilation     - Need for IV diuretics.     - Oliguria (<0.5 ml/kg/hour) as a sign of hypoperfusion of the kidneys (after volume therapy) |
| **Subgroup of patients with cardiogenic shock:**  **Additional inclusion criteria** | Additional inclusion criteria includes *both* of the following:   - - Systolic BP <90 mmHg after 60 min of adequate volume therapy or systolic BP between 90 and 100 mmHg with inotropic support by catecholamine infusion   - Signs of hypoperfusion (low-output heart failure)     - Oliguria (diuresis <0.5 ml/kg/hour)     - Cold, clammy extremities     - Reduced consciousness |
| **Exclusion criteria** | - Age below 20 years, - Heart rate above 120 bpm - Septic shock - ARDS - Creatinine >450 mol/l - Hepatic impairment - Significant mechanical outlet obstruction - Allergy against study drug medication or one of its ingredients - Anaemia (Hb < 8 g/dl) - Pregnancy |
| **Methods** | - Regional contractility or wall motion score-index is measured by echocardiography including tissue doppler imaging at baseline and 24 hours, 5 days and 6 weeks after the start of the study drug infusion.   - Infarct size measured at 6 weeks by gated spect (radioisotope teqniche). - A blood sample is frozen at baseline and after 1, 2, and 5 days and after 6 weeks after the start of the study drug infusion. BNP, lactate and inflammation markers are analysed by methods specified in the study protocol. - Hemodynamic data (Cardiac index, stroke volume, PCWP, SVRI etc.) and central venous oxygen saturation are collected by a pulmonary artery-catheter (Swan-Ganz catheter) in a subgroup of patients in cardiogenic shock. - IV inotropes are allowed to be used freely in the subgroup of patients in cardiogenic shock, but not in the other patients. If IV inotropes is needed, the patient should be included in the cardiogenic shock subgroup. If IV inotropes is needed at the clinician’s decision after the start of the study drug infusion, this should be regarded as an endpoint. - Global assessment is completed by the physician and the patient as change from baseline at 24 hours and at 5 days after the start of study drug treatment. - ”Hospitalisation” is measured according to definitions in the study protocol and mortality and angiographic data is collected. - Safety variables (adverse events, HR, BP, ECG, lab, concomitant medication) are recorded during the study. - A prospectively defined subgroup of patients in cardiogenic shock will be randomised by stratified randomisation. |
| **Study medication** | Bolus dose of 12 ug/kg for 60 minutes. The bolus dose is followed by a continuous infusion of 0,1 ug/kg/min for 24 hours. Noradrenalin must be mixed and ready for use before starting the study drug infusion. If the dose is not well tolerated (systolic BP <80 mm Hg and a drop in MAP >10 mm Hg):  Reduce the dose to 0,05 ug/kg/min. If this is not sufficient:  Start noradrenalin infusion (start dose: 0.03 g/kg/min). If this is not sufficient: Stop the infusion of the study drug.  After 24 hours the infusion is turned off abruptly.  Placebo is administered in the same way as levosimendan. |
| **Total duration of study** | The study drug infusion is 25 hours long.  There are follow-up during the first 5 days and then at 6 weeks after the start of study drug treatment. The MACE end-point and total mortality will be measured at 6 weeks and at 6 months. |

**Bacground and study rationale:**

Acute myocardial infarction is the result of a partially or fully occluded coronary artery. This results in ischemic myocardium with cell necrosis and scar tissue formation. Reperfusion therapy by thrombolysis or PCI is the key factor in modern treatment of acute myocardial infarction.

The calcium sensitizer levosimendan has been shown to increase hemodynamics and survival in patient hospitalised for decompensated heart failure (1, 2). There are limited data in patients with acute myocardial infarction. Only one major study, the RUSSLAN trial, has reported results on levosimendan in this clinical setting (3). The RUSSLAN trial was primarily a safety and dose-response trial. The incidence of ischemia and/or hypotension was similar in all treatment groups except in the highest levosimendan dose group. Levosimendan-treated patients also showed improved survival at 6 months. In the RUSSLAN trial, acute revascularization and cardiogenic shock were exclusion criteria. Thus, the effects of levosimendan in patients with myocardial infarction treated with modern reperfusion therapy are lacking.

As is the usual case for patient in cardiogenic shock, this group of patients has been excluded from all randomized trials using levosimendan. Evidence of the safety and efficacy of levosimendan in patients with cardiogenic shock is therefore also lacking even though this patient group with critically reduced left ventricular systolic function, should theoretically benefit the most.

**Hypothesis:**

Reperfusion therapy by thrombolysis or acute percutan coronary intervention (PCI) is emerging as routine treatment of acute myocardial infarction. After reperfusion of the ischemic myocardium decreased contractility is seen for several days despite of restoration of epicardial blood flow. This phenomenon is called myocardial stunning (4). The mechanisms underlying this phenomenon are partially unknown, but seem to include increased calcium overload in the myocytes during reperfusion and the production of free oxygen radicals (4). The sum of these effects leads to decreased contractility as a result of decreased calcium sensitivity.

Hypothesis: Treating patients in this critical clinical setting with the calcium sensitizer levosimendan (5) during the first hours after acute PCI will possibly improve contractility without harmful side effects. In the setting of an acute myocardial infarction with signs of decompensated heart failure, levosimendan could improve myocardial function during the stunning period, without increased oxygen consumption and risk of lethal arrhythmias. This could potentially improve patients symptoms, reduce the need for potentially harmful inotropes (6) and decrease the combined endpoint of death, new myocardial infarction and new revascularization during the first 6 month of follow-up. According to this hypothesis, levosimendan will also be able to improve markers of myocardial function and reduce markers of inflammation. In the setting of cardiogenic shock, levosimendan will be safe to use in combination with traditional inotropes. It will improve regional contractility and left ventricular function measured by echocardiography and BNP levels. It will also improve hemodynamics including tissue perfusion, measured by pulmonary artery catheterization.

**Scientific value-summarized**

The present study will provide new knowledge about the effects and safety of levosimendan in the clinical setting of acute myocardial infarction complicated by left ventricular failure in spite of modern rreperfusion therapy by acute PCI.

The study will provide new information about whether increasing the calcium sensitivity of the myofilaments and vasodilatation could improve regional contractility during the stunning period after restoriation of epicardial blood flow by PCI. The double blind, placebo controlled design makes it possible to study the effect of the active study drug on regional contractility during a time period with expected improvement of contractility in the hours after PCI due to gradually reduced stunning.

The study will contribute to already existing information about the safety of levosimendan during acute myocardial infarction with special emphasis on cardiac arrythmias, hypotension and new ischaemic episodes.

The study will provide new information about the effect of levosimendan on inflammation which has been proposed to be an important part of the stunning mechanism.

The study will gain knowledge on the use of levosimendan in patients with cardiogenic shock. This is a group of patients which is almost always excluded from clinical trials and lack of information about pharmacological treatment is striking. We (see Appenix) and others (7) have used levosimendan in this setting as add-on therapy to catecholamines, but this should be done as a part of a placebo-controlled trial. Although the expected numer of patients in cardiogenic shock in the present trial is too low to provide information regarding mortality, the study will nevertheless give information about the effects of levosimendan on regional contractility, hemodynamics, potential side-effcts and the practical approach of combining levosimendan and catecholamines.

**Methods (see study protocol):**

Patients with acute myocardial infarction undergoing acute PCI will be screened for inclusion in the study. Patients developing symptoms and signs of left ventricular heart failure will be included in the study. Patients must have a reduced myocardial viability measured by echocardiography before inclusion in the study. Patients in cardiogenic shock will be assigned to a prospectively defined subgropup by stratified randomization. The study is a randomised double-blind study with parallel groups receiving a 24 hours infusion of levosimendan or placebo. This will be done by double-blind, double-dummy teqnique. The effect of the treatment will be validated by measurement of regional contractility (echocardiography), brain natriuretic peptide (BNP), symptom score and infarct size (isotope teqnique). The effect of levosimendan on inflammation markers will also be measured.

# Study center

Ullevål University Hospital, Oslo, Norway. Ullevål University Hospital is a high-volume coronary intervention center, staffed 24-hours a day, performing 600 acute PCIs per year. In addition, about 1500 routine PCIs are done yearly. The patients included in the study will be treated and monitored in either a coronary care unit or an intensive care unit.

## Study protocol

**Patient group**

Patient with acute myocardial infarction referred to Ullevål University hospital.

**Major inclusion criteria:** Patients who are hospitalised with acute ST-segment elevation myocardial infarction (STEMI: ECG definition) subjected to acute PCI

*or*

patients with non-ST segment elevation myocardial infarction subjected to PCI within 72 hours after start of chest pain.

*and all of the following (1-3)*

- - Revascularization by PCI with opening of an occluded coronary artery or balloon dilatation of a stenotic coronary artery presumed to be culprit lesion
  - Depressed contractility of the left ventricle (left ventricle ejection fraction < 40 %) assessed by echocardiography
  - Dyspnoea at rest at screening and *at least* one of the following signs of left ventricular failure (within 48 hours after PCI):
    - Pulmonary edema
    - Signs of marked pulmonary congestion on chest x-ray
    - Need for continuous-elevated positive airway-pressure ventilation (CPAP) or mechanical ventilation
    - Need for IV diuretics.
    - Oliguria (<0.5 ml/kg/hour) as a sign of hypoperfusion of the kidneys after volume therapy.

**Subgroup of patients with cardiogenic shock:**

A prospectively defined subgroup included by stratified randomisation.

**Inclusion criteria**

Additional inclusion criteria includes *both* of the following:

- - Systolic BP <90 mmHg after 60 min of adequate volume therapy or systolic BP between 90 and 100 mmHg with inotropic support by catecholamine infusion
  - Signs of hypoperfusion (low-output heart failure)
    - Oliguria (diuresis <0.5 ml/kg/hour)
    - Cold, clammy extremities
    - Reduced consciousness

**Exclusion criteria**

- Age below 20 years,
- Heart rate above 120 bpm
- Septic shock
- ARDS
- Creatinine >450 mol/l
- Hepatic impairment
- Significant mechanical outlet obstruction
- Allergy against study drug medication or one of its ingredients
- Anaemia (Hb < 8 g/dl)
- Pregnancy

**Primary endpoints**

**Efficacy parameters**:

- - Changes from baseline to 5 days in Wall motion score-index measured by echocardiography.
  - Changes from baseline to 5 days in BNP (Brain natriuretic peptide).
  - Clinical composite at 5 days after the start of the study drug infusion, according to the physician’s global assessment measured as change from baseline to 5 days.

**Safety parameters**: Number of patients developing:

- - Hypotension: BP < 90 mm Hg or a drop in mean arterial BP > 10 mm Hg in patients with cardiogenic shock.
  - Tachycardia (heart rate above 120).
  - Atrial fibrillation.
  - Ventricular arrhythmia (VT, VF, TDP).
  - Ischemic episodes (ECG changes or chest pain demanding treatment).

# Secondary endpoints

# Efficacy parameters

- MACE: Time to death, non-fatal myocardial infarction or revascularization of the infarct related artery during the first 6 weeks and 6 month after start of the study drug infusion.
- Changes from baseline to 24 hours in Wall motion score-index measured by echocardiography
- Changes from baseline to 6 weeks in Wall motion score-index measured by echocardiography
- Changes from baseline to 24 hours in BNP
- Changes from baseline to 6 weeks in BNP
- Number of days in intensive or coronary care unit.
- Total number of days hospitalised.
- Time to re-hospitalization for decompensated heart failure.
- Clinical composite at 24 hours after the start of the study drug infusion, according to the physician’s global assessment measured as change from baseline to 24 hours.
- Infarct size measured at 6 weeks by gated spect (radioisotope technique).
- Changes of inflammation markers, haemostasis parameters and serum lactate from baseline to 24 hours, 5 days and 6 weeks.
- Changes of E/É ratio measured by echocardiography from baseline to 24 hours and 5 days.

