**In a subgroup of patient *with* cardiogenic shock:**

- Improvement of hemodynamic parameters (CI, PCWP, and SVRI) from baseline to 24 and 48 hours.
- Number of days on intra-aortic-balloon counter pulsation treatment (IABP).
- Improvement of central venous oxygen saturation.
- Improvement of kidney function measured as creatinine clearance.
- Total mortality (number of patients alive at discharge).

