**Registration of hospitalisation and MACE:**

Days in CCI/ICU and total length of stay in hospital will be measured. In-hospital mortality will be measured. Time to death, non-fatal myocardial infarction or revascularization is measured at 6 weeks and 6 month. The Norwegian death registry will be used to compare mortality at 6 month.

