**Number of patients:**

60 patients at Ullevål University hospital. A minimum of 14 patients in cardiogenic shock will be included. If necessary, the total number of patients in the study will be increased in order to reach the number of patients in cardiogenic shock.

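### Days in hospital, in ICU/CCU and on IABP are raw counts that death cuts short, with no rule for deaths, so they favour an arm with more early deaths

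*Protocol*

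**What the plan says.** Three secondary efficacy endpoints in the protocol count days spent in a state of care:

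- For all patients, the efficacy parameters under Secondary endpoints include "Number of days in intensive or coronary care unit" and "Total number of days hospitalised".
- For the shock subgroup, the list adds "Number of days on intra-aortic-balloon counter pulsation treatment (IABP").

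The section on registration of hospitalisation and MACE is the only text on how stays are recorded. It says "Days in CCI/ICU and total length of stay in hospital will be measured". The Methods row of the Protocol Summary points to definitions of hospitalisation in the study protocol, but no text shown gives one that deals with death.

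The Statistics section makes the intention-to-treat population, that is all randomised patients, the primary population for efficacy. Deaths before discharge are foreseen. The shock subgroup has the endpoint "Total mortality (number of patients alive at discharge"), in-hospital mortality is recorded, and the section on number of patients states "A minimum of 14 patients in cardiogenic shock will be included", out of a planned total of 60.

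**The concern.** As efficacy measures, these counts are read as fewer days meaning a better result. Death ends all three. A patient who dies on day 2 contributes 2 hospital days, while one who survives and goes home on day 12 contributes 12, so the worse outcome gets the better score. Because all randomised patients are analysed, those who die remain in the comparison with their short counts.

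The hypothesis section expects levosimendan to reduce a combined endpoint that includes death. If it does reduce early death, the patients it saves add days to its arm and these endpoints move against it. If it increases early death, they move in its favour. The effect should be most marked in the shock stratum, where deaths are likeliest and where the IABP count applies. Analysing survivors only would not solve this, because survival is itself a result of treatment and the comparison would no longer be a randomised one.

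**Working it through.** The plan states no figure to reproduce. The check is the text as set out above, plus arithmetic on assumed values.

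**Inputs**

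- From the protocol: raw counts, no rule for death, all randomised patients analysed, at least 14 of 60 in shock (14/60 = 23%), a 6-week (42-day) follow-up.
- Assumed, because the protocol gives none: hospital mortality 20% v 10% (whole trial) or 50% v 30% (shock), the lower rate in the levosimendan arm; death on day d = 2 to 4; survivors discharged on day s = 9 to 12, the same in both arms.

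**Formulas**, for an arm with mortality p

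- Mean days hospitalised = p·d + (1 − p)·s
- Difference between arms = (p_placebo − p_levosimendan)·(s − d)
- Mean days alive and discharged, to day 42 = (1 − p)·(42 − s)

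**Results with d = 2, s = 12**

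| Mortality, placebo v levosimendan | Mean days hospitalised | Days alive and discharged to day 42 |
|---|---|---|
| 20% v 10% | 0.2·2 + 0.8·12 = 10.0 v 0.1·2 + 0.9·12 = 11.0 | 0.8·30 = 24.0 v 0.9·30 = 27.0 |
| 50% v 30% | 0.5·2 + 0.5·12 = 7.0 v 0.3·2 + 0.7·12 = 9.0 | 0.5·30 = 15.0 v 0.7·30 = 21.0 |

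The raw count makes the lower-mortality arm look 1.0 or 2.0 days worse. The death-adjusted measure makes it 3.0 or 6.0 days better.

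**Range over the grid.** The smallest reversal is 0.10·(9 − 4) = 0.5 days and the largest is 0.20·(12 − 2) = 2.0 days. The sign is the same throughout, because every assumed death comes before the survivors' discharge.

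**Other directions**

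- Equal mortality and equal timing: the difference is 0, so there is no bias.
- Equal mortality of 20% but death on day 2 in one arm and day 4 in the other: 0.2·(4 − 2) = 0.4 days in favour of the arm whose patients die sooner.
- Mortality doubled from 10% to 20% by treatment (d = 2, s = 12): mean stay falls from 11.0 to 10.0 days, which reads as a benefit.

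**Chance variation.** I simulated 20,000 trials with 30 per arm, mortality 20% v 10%, death on day 2 and gamma-distributed stays with mean 12. The lower-mortality arm had the longer mean stay in 63%, 67%, 73% and 78% of trials for gamma shapes 1, 2, 4 and 9. That is only the sign of the difference. A two-sided t-test at 0.05 went against that arm in about 5% to 12% of trials. Days alive and discharged to day 42 favoured it in 79% to 85%.

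The figures are for hospital stay. The same formula applies to unit and IABP days, with s the survivors' days in that state. The shift in days is smaller where s is smaller, and it disappears if patients who die have already left that state.

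**The case against.** The strongest reply is that this belongs to the analysis plan. The protocol names three variables but gives no summary measure, test or scoring of deaths, and the intention-to-treat sentence says who is analysed, not how a death counts. An analysis plan that is not shown may add a rule. This stands in part: the document does not say that deaths will enter with their observed days. But the endpoint itself is written as a plain count, and changing it to a death-adjusted measure redefines the variable, which belongs in the protocol.

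Several stronger readings are tempting and are not supported:

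- *The endpoints are biased against levosimendan.* They are not biased as such. A shift needs a difference between arms in mortality or its timing, and the protocol predicts no size for one. Its section on scientific value says the shock group is too small to inform on mortality.
- *The stay has no end point.* The registration section speaks of length of stay next to in-hospital mortality, which reads naturally as the index admission, ending at discharge. What is missing is a common window and a value for deaths.
- *Excess deaths could pass unnoticed as a shorter stay.* Mortality is reported separately: in hospital, at discharge in shock, and at 6 weeks and 6 months. A reader would see the deaths, although seeing them does not correct the day counts.
- *The repair is a matter of wording alone.* Days out of hospital over 6 weeks would need readmission days from any cause. The protocol lists only time to re-hospitalisation for decompensated heart failure.

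**Conclusion.** The point holds as a conditional one. Three secondary efficacy endpoints are defined so that death improves the score, deaths are expected in this population, and nothing in the protocol says how to handle them. If early mortality or its timing differs between arms, the counts move in favour of the arm with more early deaths. On the assumed inputs the lower-mortality arm looks 0.5 to 2.0 hospital days worse. The true size depends on mortality, timing of death and stay, none of which the protocol gives. The direction rests on deaths coming before the usual discharge.

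The main endpoint (wall motion score index), the other primary endpoints and the sample size are untouched. This is a worthwhile and inexpensive improvement to secondary endpoints and does not threaten the trial's main conclusion.

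**What to change.** Redefine the three endpoints over one fixed window from randomisation, for example to 6 weeks, in all randomised patients:

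- days alive and discharged from the index admission;
- days alive and outside ICU/CCU;
- in the shock stratum, days alive and free of IABP.

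Death scores zero further days, or worst rank. State which of the two applies before unblinding. Show the raw day counts descriptively, beside mortality in each arm.

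**Cost.** Index stay, unit days, IABP days and 6-week mortality are already planned, so the main cost is a protocol amendment. Readmission days should be counted only if they are collected at the 6-week visit, which would be a small addition to the case report form. Tying the first measure to the index admission avoids depending on them.

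**Downside.** The new measures mix survival with length of stay, so the components must be reported alongside. With about 14 shock patients, roughly 7 per arm, days alive and free of IABP will be driven largely by mortality and should be read as descriptive.
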